|                                             | 
event/concurrent medication questioning will occur
 
Study Period 2 (Booster Injection):
 
At Week 23 (Visit 15), one week prior to the booster vaccination/placebo administration, the subject will attend the clinic and safety assessments will be performed.
 
At Week 24 (Visit 16), subjects will be administered a single booster vaccination/placebo.
 
At Week 25 (Visit 17), immune monitoring will be performed. Subjects will also be required to collect genital swabs for viral culture for 45 days from Week 25. Swabs will be sent to the laboratory for viral load testing, virus typing and/or sequencing.
 
At Week 28 (Visit 18), immune monitoring and safety assessments will again be performed.
 
Follow up:
 
Subjects will be contacted via the telephone at Week 36 and 42 (Visits 20 and 21). Adverse event and concurrent medications will be recorded.
 
End of Study:
 
At Week 48 (Visit 22), safety assessments will be performed.
 
Additional information:
 
Subjects will be required to suspend all HSV-2 medication during the shedding assessments and for one week prior to the Run-in shedding assessment and throughout the study period.
 
Urine pregnancy testing will be conducted for female subjects at Screening, before administration of each dose of investigational vaccine/placebo and at the End of Study Visit. If positive, a serum pregnancy test will be conducted and the study investigational vaccine/placebo will not be administered until the result of this is received. If the result of the serum pregnancy test is negative, administration of investigational vaccine /placebo will continue. If the result of the pregnancy test is positive, the subject will be withdrawn from the study.
 
Vital signs will be recorded prior to study vaccine/placebo administration and at 30 minutes and 60 minutes following each dose. Subjects will be required to remain in the clinic for at least 60 minutes after administration or longer if clinically indicated.
 
Blood samples will be collected and shipped to nominated laboratories for preparation of serum and peripheral blood mononuclear cells (PBMCs) for use in immunological analyses (T-cell and antibody responses).
 |

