 Safety assessments to be performed prior to investigational vaccine/placebo.

 Vital signs to be performed prior to investigational vaccine/placebo administration at 30 minutes and 60 minutes following each dose.

 Urine pregnancy testing will be conducted in female participants at Screening, before each administration of study vaccine and at the end of study visit. If positive, a serum pregnancy will be conducted and the vaccine will not be administered.

|               |                                                                                                                                                                                                                                                                      |
|---------------|----------------------------------------------------------------------------------------------------------------------------------------------------------------------------------------------------------------------------------------------------------------------|
|   | To be repeated as deemed necessary by site staff                                                                                                                                                                                                                     |
|   | Subject to document daily whether any HSV-2 symptoms have occurred during the shedding assessments. Following receiving the investigational vaccine/placebo, the subject to document the existence and nature of any injection site reactions that occur for 7 days. |
|   | Visit window is +/- 3 days                                                                                                                                                                                                                                           |
|   | Visit window is +/- 5 days                                                                                                                                                                                                                                           |
|  | Subjects to be either contacted via phone or visit clinic to assess swabbing technique. If subject has had difficulties in collecting swabs since Visit 2, the subject is to be re-educated.                                                                         |

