### 5.2 Inclusion Criteria

The criteria for entry into the study are:

1. Diagnosis of genital HSV-2 infection confirmed by positive HSV-2 serology or if negative a documented positive HSV-2 pathology result, AND positive PCR for HSV-2 during the Baseline Shedding Assessment prior to randomisation
2. A history of recurrent genital HSV-2 for at least 12 months AND a self-reported history of at least 3 and no more than 9 reported lesion occurrences in the 12 months prior to Screening or, if currently on suppressive therapy, in the 12 months prior to initiation of suppressive therapy.
3. Aged 18 to 50 years, inclusive.
4. Male or female. Women of child-bearing potential must be using two effective methods of contraception and agree to continue to do so from Screening, throughout Investigational vaccine/placebo dosing and for 28 days after the last dose of investigational vaccine/placebo.
5. Has voluntarily given written informed consent.

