#### 6.4.6 Pregnancy tests

Urine pregnancy testing will be conducted for female subjects at Screening, before administration of each dose of investigational vaccine/placebo and at the end of the study. If positive, a serum pregnancy test will be conducted and the investigational vaccine/placebo will not be administered until the result of this is known. If the result of the serum pregnancy test is negative, administration of study vaccine/placebo will continue. The subject will be re-educated regarding the contraception requirements for this study. If the result of the pregnancy test is positive, the subject will be withdrawn from the study.

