## **8.9 Risks for Women of Childbearing Potential or during Pregnancy**

The risks of treatment with Study Product during pregnancy have not been evaluated. Pre-menopausal women of childbearing potential will follow a medically prescribed birth control regimen or agree to abstain from heterosexual intercourse while participating in the study and for 28 days following the last dose of Study Product.

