### 8.10 Procedures to be Followed in the Event of Pregnancy

The subject must be instructed to inform the Investigator IMMEDIATELY if she becomes pregnant during the study. No further vaccinations will be administered. The Investigator should report all pregnancies to Admedus Vaccines Pty Ltd or the Contract Research Organisation (CRO) acting on their behalf within 24 hours of becoming aware of the pregnancy. Pregnancies should be reported using the form in the CRF for reporting the occurrence and outcome of pregnancies in subject enrolled in the study.

Monitoring of the subject should continue until conclusion of the pregnancy. The outcome of the pregnancy should be reported to Admedus Vaccines Pty Ltd or CRO if the study is still in progress at the end of the pregnancy. If the end of the pregnancy occurs after the study has been completed, the outcome should be reported to Admedus Vaccines Pty Ltd.

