### **10.3 Withdrawal of subjects from Study Product**

Section 8.6 provides guidance for dose modification or discontinuation of Study Product in the event of AEs or abnormal laboratory values.

If a subject permanently discontinues dosing with Study Product, for example as a result of an AE, every attempt should be made to keep the subject in the study and continue to perform the required study related follow-up and procedures.

The ideal is to continue to follow the subject for the full study period or until resolution of the adverse event. If it is not possible for the subject to remain in the study for the full study period, every attempt should be made to keep the subject in the study up to the Exit Evaluation at Day/Week . If the subject remains in the study but off study treatment, all study procedures should continue as per protocol.

If the subject will not remain in the study for all study related procedures, the Exit Evaluation should be performed wherever possible.

All subjects who discontinue study medication dosing should be followed for at least 30 days after the last dose of Study Product in order to monitor subjects for possible post-treatment events which may occur after Study Product has been discontinued.

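### The protocol gives conflicting consequences for a positive pregnancy test, so adverse-event follow-up of a dosed subject depends on which section the site reads; the contraception period is also stated two ways

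*Protocol*

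**What the plan says.** The protocol states the consequence of a positive pregnancy test in several places:

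- **Synopsis (Study procedures, Additional information) and Section 6.4.6**, in the same words: "If the result of the pregnancy test is positive, the subject will be withdrawn from the study". A positive urine test first leads to a serum test, and dosing goes ahead if the serum test is negative.
- **Table 1, footnote 5**: "If positive, a serum pregnancy will be conducted and the vaccine will not be administered". It does not mention leaving the study.
- **Section 8.10**, the section devoted to pregnancy: "No further vaccinations will be administered", followed by "Monitoring of the subject should continue until conclusion of the pregnancy". It does not mention leaving the study either.
- **Section 10.2** lists pregnancy at any time in the study among reasons that justify withdrawal. The list permits withdrawal and does not require it.
- **Section 10.3**, for subjects who permanently stop product: "every attempt should be made to keep the subject in the study and continue to perform the required study related follow-up and procedures". Section 12.1.3 repeats this.

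Section 6.4.6 schedules testing at Screening, "before administration of each dose of investigational vaccine/placebo and at the end of the study", that is, Day 0 and Weeks 4, 8, 24 and 48.

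The contraception period is also stated in more than one way. Inclusion criterion 4 runs it through dosing and "for 28 days after the last dose of investigational vaccine/placebo", and Section 5.4.1 agrees. Section 8.9 asks for birth control or abstinence "while participating in the study and for 28 days following the last dose of Study Product".

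**The concern.** All these sections agree that vaccination stops once pregnancy is confirmed. They differ on whether the subject also leaves the study.

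That difference bears on the primary endpoint, the incidence and severity of adverse events (Section 4.2). Section 8.2 records adverse events up to a subject's last day on study, so withdrawal shortens the recording period. Section 8.9 also says that risk in pregnancy has not been evaluated, which makes a vaccinated subject who becomes pregnant an informative safety case. Section 10.2 itself asks investigators to make every reasonable effort to retain subjects, except where withdrawal is for safety.

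A site working from the synopsis or Section 6.4.6 would end her scheduled contacts. A site working from Sections 8.10 and 10.3 would probably keep them. No later analysis can recover data that were not collected.

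**Working it through.** No figure in the plan needs reproducing: Section 11.1 says the sample size was set on practical grounds. The check compares the texts and then does calendar arithmetic.

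**Step 1. The texts side by side**

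| Place | Vaccination | Stays in study? |
|---|---|---|
| Synopsis; 6.4.6 | Stops | No, withdrawal is mandatory |
| Table 1, footnote 5 | Withheld | Not addressed |
| 8.10 | Stops | Monitoring continues; withdrawal not mentioned |
| 10.2 | – | Withdrawal permitted |
| 10.3; 12.1.3 | Already stopped | Yes, where possible |

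Section 8.10 does not say whether its monitoring includes the scheduled safety visits and calls, so it does not settle the matter.

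**Step 2. Follow-up lost if the synopsis rule is applied**

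Inputs: doses at Weeks 0, 4, 8 and 24 (Section 6.8.3); last visit at Week 48 (Visit 22); visit numbers from Table 1. Each test comes before that day's dose. All times are nominal, ignoring visit windows and the wait for the serum result.

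- Weeks lost = 48 − week of test
- Contacts lost = 22 − visit number of test

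| Test | Earlier doses | Weeks lost | Share of 48 weeks | Contacts lost |
|---|---|---|---|---|
| Visit 7, Week 4 | 1 | 48 − 4 = 44 | 92% | 22 − 7 = 15 |
| Visit 9, Week 8 | 2 | 48 − 8 = 40 | 83% | 22 − 9 = 13 |
| Visit 16, Week 24 | 3 | 48 − 24 = 24 | 50% | 22 − 16 = 6 |
| Visit 22, Week 48 | 4 | 48 − 48 = 0 | 0% | 22 − 22 = 0 |

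A positive test at Screening or Day 0 comes before any dose and is an exclusion (criterion 3), so no exposed subject is lost there. If the subject stops dosing but stays in follow-up, the loss is 0 weeks in every row.

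Withdrawal at Week 4 or 8 also removes both 45-day post-dose swabbing periods, which start at Weeks 9 and 25. Withdrawal at Week 24 removes the second.

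**Step 3. Weight of one subject**

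Sub-groups are 15 on COR-1 and 5 on placebo (Section 6.5). One subject is 1/15 = 6.7% or 1/5 = 20%. The protocol gives neither the number of women nor an expected number of pregnancies, so the total loss cannot be estimated.

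**Step 4. What the 30-day minimum in Section 10.3 adds**

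Section 10.3 asks for at least 30 days of follow-up after the last dose. At the Week 4 and Week 8 tests the last dose was 28 days earlier, so it adds 30 − 28 = 2 days. At the Week 24 test the last dose was at Week 8, (24 − 8) × 7 = 112 days earlier, so it adds nothing.

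**Step 5. Contraception period**

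Inclusion criterion 4 and Section 5.4.1: Week 24 + 28/7 = Week 28. Section 8.9: study participation, so to Week 48. The two differ by 48 − 28 = 20 weeks.

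**The case against.** The strongest case on the other side is that this is a small wording mismatch with limited consequences. Several parts of it stand.

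- **The loss is not total.** Section 10.4 asks for a complete final evaluation. Section 8.10 follows the pregnancy to its outcome. Section 8.2.2 keeps at-least-possibly related events reportable at any time, and Section 8.6 follows drug-related events to resolution. The subject stays in the safety analysis set (Section 11.1.1). What remains exposed is the scheduled, even-handed collection of all adverse events, related or not, which a comparison between groups needs.
- **Some texts can coexist.** Pregnancy monitoring can go on after study withdrawal. Section 10.3 is a general rule that a specific pregnancy rule could override. Even so, a mandatory rule and a permissive one for the same event are not the same rule.
- **Pregnancy is absent from the synopsis list of reasons for stopping treatment.** This is not a further contradiction, because the synopsis handles pregnancy as study withdrawal.

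A reader might infer that withdrawal after the Week 24 dose only ends data collection. The protocol does not support that. Participation restricts antiviral use (Sections 5.4, 7.2.2 and 8.8), with a bar during swabbing periods, and withdrawal lifts that restriction. Section 3.1 notes transmission from mother to child. For the same reason, asking that every non-dosing procedure continue to Week 48 would amount to choosing a clinical rule.

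**Conclusion.** The contradiction is real. The synopsis and Section 6.4.6 mandate study withdrawal; Section 8.10, Table 1 footnote 5 and Sections 10.2 and 10.3 do not. It decides whether a dosed subject positive at Week 4, 8 or 24 loses 44, 40 or 24 weeks of scheduled adverse-event follow-up. The figures assume nominal visit timing, detection at a scheduled test, and a site that applies the synopsis rule literally. In a descriptive pilot with an unknown and possibly zero number of pregnancies, this should be corrected but does not threaten the study.

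Three stronger readings do not hold:

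- **That any positive test up to Week 48 costs primary safety follow-up.** No test is scheduled between Weeks 24 and 48. A pregnancy in that interval would reach the site by self-report under Section 8.10, and Section 10.2 permits withdrawal without forcing it. A Week 48 positive falls at the last visit and loses nothing.
- **That a Week 48 positive turns a completer into a withdrawal.** Section 10.1 counts a subject as complete once all procedures are done.
- **That contraception is required only to Week 28.** Section 8.9 covers the remaining 20 weeks. The defect is the disagreement between sections.

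**What to change.** 1. Reconcile the synopsis, Table 1 footnote 5 and Sections 6.4.6, 8.10, 10.2 and 10.3 so that one consequence of a confirmed positive pregnancy test applies throughout.
2. In that text, state the end of vaccination separately from the end of study data collection.
3. Say whether the monitoring in Section 8.10 includes the adverse-event and serious-adverse-event contacts already scheduled, so that primary safety data on exposed subjects do not depend on which section a site follows.
4. Reconcile inclusion criterion 4 and Sections 5.4.1 and 8.9 to one contraception period.

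Which withdrawal rule and which contraception period are right is a clinical decision for the sponsor and investigators, and none is proposed here. The cost is a wording amendment with ethics committee submission under Section 12.1.5; reconciling the text needs no new visits, tests or subjects.

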**LIST OF TABLES****GLOSSARY OF ABBREVIATIONS**

|          |                                                                     |
|----------|---------------------------------------------------------------------|
| AE       | Adverse Event                                                       |
| ADR      | Adverse Drug Reaction                                               |
| ALP      | Alkaline Phosphatase                                                |
| ALT      | Alanine Transaminase                                                |
| AST      | Aspartate Transaminase                                              |
| Beta-HCG | Beta Human Chorionic Gonadotropin                                   |
| BMI      | Body Mass Index (weight in kg divided by height in m  ) |
| BP       | Blood Pressure                                                      |
| cGMP     | Current Good Manufacturing Practice                                 |
| CI       | Confidence Interval                                                 |
| CMI      | Cell-mediated Immunity                                              |
| COA      | Certificate of Analysis                                             |
| CRF      | Case Report Form                                                    |
| CPMP     | Committee for Proprietary Medicinal Products                        |
| CRO      | Clinical Research Organisation                                      |
| CS       | Clinically Significant                                              |
| CSR      | Clinical Study Report                                               |
| CTN      | Clinical Trial Notification                                         |
| CV       | Coefficient of Variation                                            |
| d        | Day                                                                 |
| DBP      | Diastolic Blood Pressure                                            |
| DIFF     | Differential White Blood Cell count                                 |
| DNA      | Deoxyribonucleic Acid                                               |
| ELISA    | Enzyme-linked immunosorbent assay                                   |
| ELISPOT  | Enzyme-linked immunosorbent spot assay                              |
| EOS      | End of Study                                                        |
| FBC      | Full Blood Count                                                    |
| FDA      | Food and Drug Administration (US)                                   |
| GCP      | Good Clinical Practice                                              |
| GFR      | Glomerular Filtration Rate                                          |
| GGT      | Gamma Glutamyltransferase                                           |
| GH       | Genital Herpes                                                      |
| GLP      | Good Laboratory Practice                                            |
| gD2      | Envelope glycoprotein D of HSV serotype2                            |
| GMT      | Geometric Mean Titre                                                |
| Hb       | Haemoglobin                                                         |

|        |                                                                                                                       |
|--------|-----------------------------------------------------------------------------------------------------------------------|
| Hct    | Haematocrit                                                                                                           |
| HIV    | Human Immunodeficiency virus                                                                                          |
| Hep B  | Hepatitis B                                                                                                           |
| Hep C  | Hepatitis C                                                                                                           |
| HPC    | High Positive Control                                                                                                 |
| HR     | Heart Rate                                                                                                            |
| HREC   | Human Research Ethics Committee                                                                                       |
| HSV    | Herpes Simplex Virus                                                                                                  |
| IB     | Investigator's Brochure                                                                                               |
| ICH    | International Conference on Harmonisation of Technical Requirements for Registration of Pharmaceuticals for Human Use |
| Inj    | Injection                                                                                                             |
| IUD    | Intrauterine device                                                                                                   |
| ITT    | Intention to Treat                                                                                                    |
| LFT    | Liver Function Test                                                                                                   |
| LLPC   | Lower Limit Positive Control                                                                                          |
| LOQ    | Limit of Quantification                                                                                               |
| LPC    | Low Positive Control                                                                                                  |
| NCS    | Not Clinically Significant                                                                                            |
| OECD   | The Organisation for Economic Co-operation and Development                                                            |
| OTC    | Over-the-counter                                                                                                      |
| PBMC   | Peripheral blood mononuclear cells                                                                                    |
| mcg    | Microgram                                                                                                             |
| MedDRA | Medical Dictionary for Regulatory Activities                                                                          |
| MPC    | Mid Positive Control                                                                                                  |
| NA     | Not applicable                                                                                                        |
| ND     | Not Done                                                                                                              |
| NHMRC  | National Health and Medical Research Council                                                                          |
| NOAEL  | No Observable Adverse Effect Limit                                                                                    |
| NR     | Not Recorded                                                                                                          |
| NRQ    | Test Not Required                                                                                                     |
| NS     | Sample Not Obtained                                                                                                   |
| NTC    | Nature Technology Corporation                                                                                         |
| PICS   | Pharmaceutical Inspection Co-operation Scheme                                                                         |
| PC     | Positive Control                                                                                                      |
| PP     | Per Protocol                                                                                                          |
| PSCP   | Plate-Specific Cut Point                                                                                              |
| PT     | Preferred Term                                                                                                        |
| SAE    | Serious Adverse Event                                                                                                 |
| TEAE   | Treatment Emergent Adverse Event                                                                                      |

|        |                                  |
|--------|----------------------------------|
| TGA    | Therapeutic Goods Administration |
| U&E    | Urine and Electrolytes           |
| ULQ    | Upper Limit of Quantification    |
| UNK    | Unknown                          |
| US/USA | United States (of America)       |
| Vacc   | Vaccination                      |
| WHO    | World Health Organisation        |
| WMA    | World Medical Association        |

